#### Sample size and selection method

To carry out the main objective of the study, sample size calculation will be performed according to the following parameters: detection of a difference greater than or equal to 10% between the two groups in regard to smoking cessation, a proportion of 5% of smoking cessation in one of the groups accepting an alpha risk of 0.05 and a beta risk of 0.10 in a bilateral contrast, 187 smokers are required in the control group and 187 smokers in the intervention group. It is assumed that 5% of smokers will withdraw the study.

### Study variables

The study data will be collected using a structured questionnaire and data collection sheets specifically designed for this objective. The structured questionnaire will include the following data: sociodemographics (age, sex, etc.), clinical history, smoking habit, respiratory symptomatology, smoking dependence test and smoking cessation motivation test. The data collection sheets will include information related to the spirometric results, peak expiratory flow rate and the carbon monoxide test when performed.

The following variables will be collected on forced spirometry, reference values using the ATS reference equations will be used:

- Forced vital capacity (FVC): a result ≥ 80% of the reference value will be considered normal.

- Forced expiratory volume in the first second (FEV1): a result ≥ 80% of the reference value will be considered normal.

- FEV1/FVC Index: a results ≥ 70 of the absolute values will be considered normal.

Spirometry defined by FEV1/FVC < 70% will be considered as forced spirometry with an obstructive pattern. A restrictive pattern will be that with FEV1/FVC values ≥ 70% and an FVC <80% and a mixed pattern will be defined with spirometry values of FEV1/FVC <70% and FVC <80%.

- Forced expiratory flow between 25% and 75% or mean expiratory flows (FEF 25-75%): normal results will be considered as > 60% of the reference value.

- Bronchodilator test (BDT): will be considered positive when the FEV1 after the BDT increases a percentage ≥ 12% and ≥ 200 ml in absolute values.

The following tests will also be carried out:

- Pulsioxymetry.

- Anthropometric variables: height and weight.

The following data will be collected using a questionnaire and will be compared with revision of the clinical histories in each of the phases:

- Usual symptomatology: expectoration, cough, presence of wheezing, dyspnoea.

- Sociodemographic variables: age, gender, occupation, level of education, municipality of residence and site of home (rural, semi-urban, urban).

- Exposure to tobacco (measurement in packs / year), years smoking, age at initiation of smoking, current smoking intake (measurement in cigarettes / day).

- History of disease and active medication.

### Procedures

During the selection visit the primary care physician will inform the candidates for participation as to the nature of the study and will offer them the possibility to participate in the study. If the patient agrees, informed consent will be requested, and a series of tests will be indicated (spirometry, peak expiratory flow rate, smoking dependence test, smoking cessation motivation test and a structured questionnaire on sociodemographics data, history of disease, smoking habit, respiratory symptomatology, etc).

On visit 0, the primary care physician will give a brief structured smoking cessation advice to all patients combined with a detailed and structured discussion of the spirometric results.

After this visit the patients will be randomised in two arms (control and intervention groups). Randomisation will be performed using a computer programme. Randomisation will be carried out by the Coordinating Centre.

Both groups will be followed up by telephone at three (visit 1) and six months (visit 2) and at one-year (visit 3) and two-year(visit 4). During the follow up visits brief structured smoking cessation advice will be reinforced in the control group but the spirometric results will not be discussed. In the intervention group brief structured smoking cessation advice will be reinforced with a detailed structured reminder discussion of the results obtained from the spyrometry of visit 0. Follow up visits 1 and 2 will be undertaken by telephone and the patients will be asked about their smoking habit and will be given a brief questionnaire.

One month before visits 3 and 4 both groups will undergo the same series of tests performed prior to visit 0 with the exception of the peak expiratory flow rate. Spirometry will be done only in the intervention group.

On visits 3 and 4, the same intervention will be done. On both visits 3 and 4 all the participants who report smoking withdrawal will undergo the carbon monoxide test.

### Analysis plan

To achieve the first objective the rates of withdrawd and reduction of the smoking habit of the two groups will be compared at 6, 12, and 24 months.

To achieve the second objective the sensitivity, specificity and positive and negative predictive values of peak flow compared to spirometry will be determined.

For the third objective, the proportion of COPD and the severity of air flow limitation will be determined according to different study variables (age, sex, smoking habit, symptoms...).

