## Methods/Design

### Study Objectives

#### Main objective

To evaluate the effectiveness of regular reporting of spirometric results combined with a smoking cessation advice by a primary care physician on smoking quit rate in adult smokers.

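### The trial is sized for one comparison of smoking cessation, but no visit is fixed for it and the analysis plan compares the groups at three times without ranking them

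*Protocol article*

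**What the plan says.** The Main objective section asks about the effect of regular spirometry reporting "combined with a smoking cessation advice by a primary care physician on smoking quit rate in adult smokers". That is one outcome, with no time point.

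The section on sample size and selection method plans for "detection of a difference greater than or equal to 10% between the two groups in regard to smoking cessation". The reference quit rate is 5% in one arm, the test is two-sided at 0.05, and power is 90%. The stated result is that "187 smokers are required in the control group and 187 smokers in the intervention group". This is again one outcome with no time point, and alpha is not divided.

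The Analysis plan serves the first objective as follows: "the rates of withdrawd and reduction of the smoking habit of the two groups will be compared at 6, 12, and 24 months". It names no primary comparison and no order among the comparisons. Reduction in smoking appears here but in neither the main objective nor the sample size.

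The Procedures section places the 3- and 6-month contacts on the telephone. It calls for the carbon monoxide test in reported quitters at the 12- and 24-month visits only. The Abstract says that cessation will be tested with carbon monoxide and does not single out a visit.

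**The concern.** A sample size for one test at the full alpha of 0.05 is valid for one named comparison. Here the article sets out several comparisons for the same objective and does not say which one the calculation belongs to. Two things follow.

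- **The answer can be chosen late.** If the arms differ at one visit and not at another, nothing in the article says which result answers the main objective. The choice could then be made after the results are known.
- **The design assumption has no date.** A quit rate of 5% or 15% means little without a time. The Background cites 70% relapse in the first year among smokers in general, so the level of the quit rate depends on when it is measured. The planned 90% power is therefore not tied to any visit.

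The comparisons are also not interchangeable. Cessation at 6 months is telephone self-report, whereas at 12 and 24 months it is verified. Exposure differs too: only the 24-month assessment comes after both telephone reminders and a completed 12-month visit with repeat spirometry.

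**Working it through.** **Inputs from the protocol article.** Control rate 5%; difference 10 points, hence 15% in the other arm; two-sided alpha 0.05; power 90%; 187 per arm (all from the sample size section). Comparison times 6, 12 and 24 months (Analysis plan). Carbon monoxide verification at 12 and 24 months only (Procedures). The article gives no correlation between results at different visits, so the correlations below are assumptions.

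**Step 1: reproduce the stated sample size.** Pooled-variance formula, with mean rate 0.10:

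n = [1.960·√(2·0.10·0.90) + 1.282·√(0.05·0.95 + 0.15·0.85)]² / 0.10²

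= [0.8315 + 0.5361]² / 0.01 = 187.05 per arm

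This rounds up to 188, against 187 stated. Power at 187 per arm is 90.0%. The article's figure is thus the size for **one** two-sided test at the full 0.05, and the arithmetic is sound.

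**Step 2: count the comparisons that could answer the main objective.**

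| Reading of the Analysis plan | Comparisons |
|---|---|
| Verified cessation only (12 and 24 months) | 2 |
| Cessation at all three times (adds 6-month self-report) | 3 |
| Cessation and reduction at all three times | 6 |

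The main objective and the sample size section both speak of cessation, so two or three is the fair count.

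**Step 3: chance of at least one false positive.** This assumes that each comparison is tested at two-sided 0.05, that any one significant result counts as success, and that there is no true effect. For k independent tests it is 1 − 0.95^k: 0.0975 for two, 0.1426 for three and 0.2649 for six. For correlated tests, equicorrelated normal test statistics were used:

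| Assumed correlation | 2 tests | 3 tests | 6 tests |
|---|---|---|---|
| 0 (upper end) | 9.8% | 14.3% | 26.5% |
| 0.5 | 9.1% | 12.5% | 20.7% |
| 0.8 | 7.8% | 9.8% | 13.9% |
| 0.9 | 7.0% | 8.4% | 10.8% |

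Quit status in the same people at successive visits is likely to be positively correlated, so the independence row is a bound and not an expectation. Every cell exceeds 5%.

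**Step 4: compare the remedies.** Naming one primary comparison keeps alpha at 0.05 and n at 187–188 per arm. Splitting alpha equally (Bonferroni) instead gives:

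| Co-equal tests | Alpha each | Power at 187 per arm | n per arm for 90% |
|---|---|---|---|
| 2 | 0.0250 | 84.0% | 222 |
| 3 | 0.0167 | 80.0% | 241 |
| 6 | 0.0083 | 72.3% | 275 |

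Bonferroni is conservative for correlated tests, so these losses are upper limits.

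**The case against.** The best defence has four parts.

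- **Cessation is already the outcome.** The objective and the sizing both say so, and a positive result on reduction would not answer the stated question. This stands. A reader might infer from the Analysis plan that six tests of equal rank decide the trial and that the error rate is 26%. The documents do not support that: it needs reduction to count as an answer to an objective that does not mention it, and independence among repeated measures on the same people.
- **The article says only that rates will be compared.** It states no test, no alpha per comparison and no rule that one significant result is enough. A single longitudinal model would also fit the sentence. This stands in part: the percentages are conditional on a success rule that the article does not state. It does not remove the gap, because no rule of any kind picks the result that answers the objective.
- **This is a condensed article.** A multiplicity method or testing order may properly sit in a full protocol or analysis plan that is not shown, and its absence is not held against the trial. But the article does state how the main objective will be judged, and that statement does not match the single comparison it was sized for.
- **Verification points to the visit.** Carbon monoxide testing narrows the field to 12 and 24 months but does not choose between them.

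A reader might also infer that 24 months must be the primary time point because the intervention is complete only then. The documents do not settle this. The only between-arm quit rates cited (13.6% against 6.4%, in the Background and Discussion) are at 12 months, and nothing links the 5%/15% assumption to 24 months. Nor does the cited relapse rate show that the difference between arms will change from visit to visit; it concerns the level of quitting.

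**Conclusion.** The point holds in this form: one cessation comparison was sized, no visit was fixed for it, and the Analysis plan offers several comparisons without ranking them. With cessation as the outcome, the chance of at least one false positive is about 7–10% for the two verified time points and 8–14% when the 6-month self-report is added, against a planned 5%. These ranges rest on testing each comparison at 0.05, letting any one count as success, and correlations from 0 to 0.9, none of which the article states. They count false positives in either direction. The sample size arithmetic is not at fault. The fault is that the 5% error rate and the 90% power attach to no identified comparison. This bears on the main claim of the trial and should be settled before any outcome data are seen.

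**What to change.** Before data are seen, add a few lines to the Analysis plan and the sample size section:

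1. Name carbon-monoxide-verified cessation at **one** visit as the sole primary endpoint, tested at two-sided 0.05. Whether that is 12 or 24 months is for the investigators to choose, with a stated reason. Twelve months matches the comparison that the article cites; 24 months reflects the full intervention.
2. State that the 5% and 15% rates apply at that visit, and check that they are still plausible there.
3. Label verified cessation at the other visit as secondary.
4. Label 6-month self-reported cessation and all reduction results as supportive, reported with confidence intervals.

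The sample size is unchanged. The small cost is that results at the non-primary time points, and results for reduction, cannot support the main claim on their own. If the investigators prefer to keep two or three co-equal time points, the alpha split in the working shows the price: power of about 84% or 80% at 187 per arm, or 222 or 241 per arm to keep 90%.

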### Ethical considerations

The participants will be informed of the objectives of the study and the activities related to their participation in the study: number of visits, complementary tests, information of the results. The informed consent will describe the ethical conditions and the participant's right to intimacy, anonymity, confidentiality, withdrawal and information. Patients in whom a previously undiagnosed disease is detected will be provided with the usual diagnostic and therapeutic methods available through their reference physician who will be responsible for integrating the information and providing the best therapeutic and diagnostic options to the patient.

The data will be included in a database for data management with programmes of statistical analyses in which no reference will be made as to the identity of the subjects. Data confidentiality and anonymity will be ensured according to Law 15/1999 on data confidentiality during both the execution of the project and in the presentations and publications derived therewith. The investigators are committed to respecting the norms of good clinical practice, as well as the requirements of the Helsinki Declaration.

Authorisation will be requested from the directors of all the primary care centres and participating departments to access the clinical histories. The rules of the Catalan Health Institute with respect to access to clinical information for investigation will be fully respected.

This study has been approved by the Ethical Committee of Clinical Investigation of the Primary Care Research Institute Jordi Gol (Barcelona, Spain) on May 26^th ^2010.

## Discussion

The results of this study will provide better knowledge on how the results obtained with spirometry influence smokers in relation to the rate of withdrawd and aspects little known such as the use of the spirometry results to reinforce repeated and reminder brief structured antismoking advice.

The use of spirometry as a motivational tool to cease smoking currently continues to be very controversial. In 2007, Wilt et al [31] published a systematic review of the role of spirometry to increase the rates of smoking cessation and concluded that the current evidence available is insufficient to determine the benefit obtained on rates of smoking cessation with the use of spirometry compared with other cessation methods.

Of all the studies reviewed only one clinical trial evaluated the benefits of the use of spirometry with negative results. Later in 2008, Parkes et al [30] published a study in which a benefit was found in the reduction of smoking using the pulmonary age achieved in the spirometry versus the real age as the intervention. The rate of smoking abandonment achieved at 12 months was 13.6% in the intervention group versus 6.4% in the control group, with a difference of 7.2% with a confidence interval of [2.2-12.1].

Previous observational studies such as that by Gorecka et al [28] observed a benefit in the rate of smoking cessation using the results obtained in spirometry, particularly in patients with chronic airflow obstruction.

On the other hand, we expect the rate of participation in the present study to be high, based on the experience reported in previous studies, especially taking into acocunt that it is the primary physician of the patient who offers the possibility of participating and that participation does not imply invasive tests or pharmacological interventions.

With regard to the validity and reliability of the data collected, the difficulty and variability of some of the tests requested in the study for both the health care personnel as well as the patient (i.e. performing spirometry) are of note. Thus, consensus meetings among the professionals performing the study tests will be held with the aim of homogenising criteria and their practice. The SEPAR recommendations for performing forced spirometry will be followed. Likewise, meetings with the primary care physicians are foreseen to standardise the methodology of the interventions proposed in both groups of patients. In regard to the brief structured advice, the intervention recommended by the Smoking Group of the Spanish Society of Family and Community Medicine will be used.

Lastly, to reduce variability due to the measurement tools, it has been proposed that all the spirometers, peak flows and carbon monoxide tests used in the study be the same model and trademark.

In conclusion, we believe that the results of this study will provide better knowledge of the usefulness of spiromery in the increase in the currently controversial rate of smoking cessation and the utility of repeated use of brief structured advice in increasing and maintaining these rates over time.

## List of abbreviations

ATS: American Thoracic Society; BDT: Bronchodilator test; COPD: Chronic Obstructive Pulmonary Disease; CRF: Case report form; EPI-SCAN: The epidemiologic study of COPD in Spain; FEV_1_: Forced Expiratory Volume in the first second; FVC: Forced Vital Capacity; GOLD: Global Initiative for Chronic Obstructive Lung Disease; IBERPOC: Epidemiological study of chronic obstructive pulmonary disease in Spain; ICD: International Classification of Diseases; MRC: Medical Research Council; RR: Relative Risk; SEPAR: Sociedad Española de Neumología y Cirugía Torácica (Spanish Society of Pneumology and Chest Surgery); WHO: World Health Organization.
